## Abstract

**Background:**

Outdoor play supports children’s physical, social, and cognitive development; yet, opportunities are declining as indoor, screen-based childhoods become the norm. Early Learning and Child Care (ELCC) centers are key settings for promoting outdoor play, but limited evidence exists on the health and developmental outcomes of licensed nature-based ELCC programs, particularly for children with and those without disabilities.

**Objective:**

The Sending Preschoolers Outside (SPROUT) and SPROUT-able studies aim to examine the impact of one of Canada’s first purposely designed and built licensed outdoor-focused ELCC programs. The primary objective is to examine the health and developmental outcomes of children aged 10‐59 months, with and those without disabilities, attending an outdoor-focused, full-day licensed ELCC program compared to those in conventional (eg, not outdoor-focused) ELCC settings. Secondary objectives are to (1) examine educator job satisfaction, health, well-being, and attitudes toward teaching outdoors for children with and those without disabilities; (2) examine caregiver beliefs and attitudes toward children’s participation in outdoor play and learning; and (3) identify barriers and facilitators to outdoor play and learning for children with and those without disabilities (ie, the SPROUT-able substudy) in an outdoor-focused ELCC program.

**Methods:**

This prospective longitudinal open cohort study follows children, caregivers, and educators over 3 years. Participants are recruited from 1 outdoor-focused (experimental) and 3 conventional (usual care) ELCC centers in Ontario, Canada; all sites are licensed. Assessments occur every 6 months and include direct measures of children (eg, anthropometry, motor skills, and accelerometry) and caregiver and educator questionnaires. Mixed-effects modeling will examine changes over time and between groups (experimental vs usual care).

**Conclusions:**

By combining a holistic and comparative approach with a focus on children with and those without disabilities, the SPROUT and SPROUT-able studies will generate comprehensive evidence to inform ELCC practice and policy in Canada and internationally. This model within Canada provides timely evidence on outdoor-focused ELCC delivery, integrating disability inclusive outdoor play into ELCC settings, and has the potential to guide meaningful improvements in child development, educator well-being, and community health.

## Introduction

Outdoor play is essential for healthy child development, with evidence of positive changes in physical, mental, and social-emotional health [1-4]. However, societal changes such as screen-based entertainment and rising concerns over children’s safety have led to more time spent indoors and less outdoor play [3]. With more than half of children in Canada attending licensed Early Learning and Child Care (ELCC) programs [5], outdoor-focused ELCC programs (ie, licensed ELCC programs that prioritize outdoor and nature play, beyond the minimum licensing requirement) provide an opportunity to reintroduce outdoor play in early childhood. Although children remain the central focus of such programs, evidence suggests that engaging in outdoor play also benefits adults’ physical and mental health [4]. As a result, outdoor-focused ELCC programs may offer a strategy to support early childhood educators’ (herein referred to as “educators”) well-being. Emerging findings from the United Kingdom indicate that outdoor-focused programs are associated with improved educator well-being and professional engagement and development [6], suggesting potential contributions to educator retention, job satisfaction, and the overall quality of care. Taken together, the potential benefits for both children and educators reinforce the value of outdoor play in ELCC programs and the need to increase the availability of programs that support access to outdoor play in nature.

In Ontario, Canada, licensed ELCC programs are required to provide a minimum of 2 hours of outdoor play per day for children in 6 or more hours of care, weather permitting, unless otherwise exempted by a caregiver (biological or nonbiological, as well as any adult who serves as the child’s primary caregiver) or physician [7]. Despite this requirement, a recent systematic review and meta-analysis found that across 26 studies reporting on outdoor time in conventional ELCC centers (ie, licensed center-based ELCC programs primarily delivered indoors), children spent on average 45 minutes outdoors, with some programs reporting as little as 10 minutes per day [8]. The prioritization of indoor over outdoor time in ELCC settings is problematic, as research shows children are more active and less sedentary when outdoors [9], contributing to positive health and developmental benefits. It is possible that indoor time is prioritized in ELCC settings due to the perception that quality learning can only occur inside, despite a growing body of evidence to the contrary [10], and that outdoor time is for leisure pursuits only [11]. Other factors, such as temperature, climate, air quality, accessibility, perceived danger, licensing restrictions, and lack of preservice training in outdoor play, may further discourage educators from bringing children outdoors for prolonged periods of time. Given the potential benefits of outdoor time and play for children’s and educators’ overall health and well-being, efforts are needed to challenge preconceived ideas about the outdoors and promote outdoor play and learning in ELCC programs.

Outdoor play during ELCC hours is even less common for children with disabilities. For example, in a study conducted in the United States, children with disabilities spent 80% of their time at ELCC indoors, with most of their indoor activity being sedentary [12]. For children with disabilities, outdoor built and social environments are often designed in ways that limit their participation in active play [13-16]. Barriers in the built and social environments in the outdoors result in children with disabilities being excluded from outdoor play and learning experiences. Further, caregivers of children with disabilities may feel hesitant to have their child engage in outdoor play due to the inherent or perceived risk [17,18]. Spending time outdoors is beneficial to all children, including children with disabilities [1,2,19], and therefore, it is critical that efforts seeking to increase outdoor-focused ELCC programs are inclusive and accessible to children with and those without disabilities attending ELCC.

Shifting the overall mindset about outdoor play and learning for children with and those without disabilities requires a stronger evidence base to support outdoor-focused ELCC programs. Research on outdoor-focused ELCC is sparse; however, preliminary findings from an American pilot program suggest that outdoor-focused ELCC programs equally prepare children for school while also facilitating more diverse learning and skill acquisition, compared to conventional ELCC programs [20,21]. More robust research, and within a Canadian context, is required to confirm these preliminary observations and to determine the efficacy of outdoor-focused ELCC programs for promoting healthy child development and learning, educator health and well-being, and the relative benefits and risks associated with outdoor play for children with and those without disabilities.

The Sending Preschoolers Outside (SPROUT) study is a 3-year, multicomponent study that seeks to compare an outdoor-focused ELCC program to conventional non–outdoor-focused ELCC programs in Ontario, Canada. It is designed to understand whether and how outdoor-focused ELCC programs contribute to child health and development and to explore the potential benefits to educators and families. The primary objective of this study is to examine the relationship between attending an outdoor-focused, full-day licensed ELCC program and the physical, cognitive, and social-emotional development of children with and those without disabilities aged 10‐59 months, compared to children attending conventional ELCC programs. The secondary objectives of this study are to (1) examine educator job satisfaction, health and well-being, and beliefs and attitudes toward teaching in outdoor environments for children with and those without disabilities between the 2 types of ELCC programs; (2) examine caregiver beliefs and attitudes toward children’s participation in outdoor play and learning between the 2 types of programs; and (3) understand the barriers and facilitators to outdoor play and learning at an outdoor-focused ELCC center for children with and those without disabilities through the substudy “SPROUT-able.”

## Methods

### Study Design

This study uses a 3-year, prospective longitudinal (open) cohort design to compare (1) child development (physical, social-emotional, and cognitive) and children’s movement behaviors; (2) educator health and well-being; (3) educator job satisfaction and attitudes and beliefs toward outdoor play and learning; and (4) caregivers’ attitudes and beliefs toward outdoor play and learning between those at an outdoor-focused versus conventional full-day licensed ELCC program. We use a continuous recruitment approach (open cohort), whereby families and educators are invited to participate in the study leading up to either of the 2 annual data collection time points [22].

### Ethical Considerations

This study has received institutional research ethics board approval (#23/108X). Caregiver-child dyads and educators consent to 1 year of the study and are encouraged to reenroll for up to 2 years as long as the child remains at the center (refer to Figure 1 for study timeline).

**Figure 1. F1:**
[figure not shown]
SPROUT (Sending Preschoolers Outside) study timeline.

### Participants and Settings

Caregiver-child dyads are eligible to participate if children are between the ages of 10‐59 months at baseline, attend a participating ELCC center for 6 or more hours per day, 3 or more days per week, and if the caregiver can read, write, and understand English and/or French. Children with and those without disabilities will be eligible to participate in this study and efforts will be made to ensure study procedures and instruments fit the needs and abilities of children with disabilities. Educators are eligible if they are currently employed at a participating ELCC center, and they can read, write, and understand English and/or French. Participants are recruited from 2 types of ELCC programs: outdoor-focused (experimental) and conventional programs (usual care). The experimental and usual care programs are both governed by the same childcare organization and are licensed under the same provincial regulations. Given this, the centers are comparable in terms of cost per day, staffing ratios, and mealtime and nap protocols. The main difference between the centers lies in how the centers deliver the early years curriculum and where programming takes place. Details of the experimental and conventional centers’ programs, including setting, curriculum, and time outside, are detailed below.

The outdoor-focused ELCC center serves as the experimental group. This center prioritizes extended outdoor play and learning, with children spending the majority of the day outside year-round, regardless of the weather. The center is situated on 500 acres of forested land that children explore daily for learning and play. This expansive natural environment features a thick canopy of tall, established trees that provide significant shade, as well as a rich and diverse landscape with largely natural, grassy ground cover. Tree species are well mixed and include native varieties such as sugar maples, oaks, and several coniferous species. The terrain is varied, with exposed roots, rocky sections, and small but steep elevation changes, alongside wetlands and visible rock deposits that contribute to the site’s natural character and afford diverse sensory and physical experiences.

Each class has a designated “outdoor learning space” within the forested area. The infant group (<18 months) outdoor space is located closer to the building than those of the toddler (18‐30 months) and preschool (30‐71 months) groups; however, all classes have the flexibility to move beyond these areas depending on weather conditions and children’s emerging interests (Figure 2). Educators establish strong relationships with children on the land, setting clear boundaries that support safe supervision while still allowing for autonomy and exploration. The outdoor learning environments are intentionally designed to support inquiry-based and play-based learning. Natural and thoughtfully introduced provocations are embedded throughout the forest to spark curiosity and investigation. Features of the outdoor space include a fire circle, a sheltered eating area, picnic tables, climbing structures (eg, pallets and rope ladders), a secondary stick-built structure, and a rock wall that helps define boundaries. Daily experiences often include mud kitchen play, water and puddle exploration, gardening, and searching for insects and other small creatures (eg, salamanders, worms, and slugs). Natural materials such as sticks, rocks, and plants play a central role in children’s play and learning, supporting creativity, problem-solving, and physical engagement. The curriculum, while guided by the provincial early learning framework [22], emphasizes exploration, creativity, resilience, and environmental stewardship through immersive experiences in nature. Children are encouraged to engage with natural materials, ask questions, and observe ecological processes, such as plant growth and seasonal changes. Learning is child-led, play-based, and developmentally appropriate, with a strong emphasis on sensory experiences, movement, and connection to the natural world. Educators at the outdoor-focused ELCC typically hold specialized training, such as the Child and Nature Alliance of Canada’s Forest Practitioner certification or the Algonquin College Play, Learn and Teach Outdoors certificate. The educator team supports extended outdoor engagement through practices such as outdoor meals and snacks when feasible, as well as outdoor diapering routines for younger children. Indoor environments are used primarily for meals, rest, transitions, and as a safe refuge during extreme weather conditions (eg, excessive heat, severe cold, or thunderstorms).

**Figure 2. F2:**
[figure not shown]
Images of the outdoor space at the outdoor-focused Early Learning and Child Care program (ie, experimental site).

Three conventional ELCC centers will serve as the usual care control group. These centers provide conventional programming with scheduled outdoor time typically meeting the regulated amount of outdoor time, a minimum of 2 hours a day (eg, 60 minutes, twice daily) in defined play areas (eg, playground, fenced-in grass, and fenced-in pavement or rubber spaces; Figure 3). Programming follows more structured routines with educator-led activities, guided by the same provincial early learning framework that the experimental site follows [23]. Physical environments include standard play materials and fixed playground equipment. The 3 conventional ELCC centers are located in different settings, one in an urban area inside an apartment building and is licensed for 49 children (10 infants, 15 toddlers, and 24 preschoolers). One is located in an urban area in the basement of a church and is licensed for 39 children (15 toddlers and 24 preschoolers), and one is in a suburban neighborhood attached to an elementary school and is licensed for 31 children (15 toddlers and 16 preschoolers); this site also has a kindergarten and school-age program. All locations (including the experimental location) are part of the Canada-wide ELCC program, which in Ontario in 2026 means that the childcare fee is capped at CAD $22.00 (US $15.50) per day.

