**Figure 3. F3:**
[figure not shown]
Images of the outdoor space at the conventional Early Learning and Child Care programs (ie, usual care sites).

A priori power analysis was conducted using G*Power (Heinrich-Heine-Universität Düsseldorf) to estimate the sample size required to detect meaningful group differences over time for the primary objective of the study (ie, child outcomes). Given the complexity of general linear mixed-effects models and the limited availability of accessible power calculation tools for these models, a repeated-measures ANOVA with a within-between interaction was used as an approximation. This approach allows for estimating power to detect changes within participants over 3 time points and differences between 2 groups (experimental vs usual care). The calculation assumed a small effect size (*f*=0.20), a power of 0.80, and an alpha level of .05. This choice aligns with findings from systematic reviews indicating that ELCC interventions often yield small but statistically significant effects on children’s development [24]. Based on these parameters, the estimated required sample size is 42 child participants (21 per group). While our primary analyses use general linear mixed-effects models, this conservative ANOVA-based estimate provides a reasonable benchmark for planning purposes and may underestimate statistical power. Given the open cohort design, in which participants may enter and exit over time and contribute varying numbers of observations, precise specification of variance and correlation parameters is challenging at the design stage. In the absence of prior data, assumptions were therefore based on conservative estimates. To further strengthen these estimates, an internal pilot approach will be used whereby preliminary data from the first year of the study (ie, Wave 1: T0, T1, and T2) will be used to estimate key parameters (eg, variance components and within-subject correlation). These estimates will inform a refined assessment of sample size and statistical power for the remaining study period. This process will not involve formal hypothesis testing and will not affect the integrity of the primary analyses. The current sample size estimation is treated as a minimum threshold. In practice, we aim to enroll 100% of children attending the outdoor-focused ELCC center (ie, experimental site) and seek to match this number across the usual care sites. Therefore, we anticipate a substantially larger sample size that will improve the precision and generalizability of our findings [25].

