Descriptive statistics are used to summarize participant characteristics and all primary measures, including developmental assessments, movement behaviors, caregiver attitudes, support behaviors, and educator outcomes. Means and SDs are reported for continuous variables, and frequencies and percentages for categorical variables. General linear mixed-effects models will be used for the primary objective and secondary objectives 1 and 2 to examine differences in change over time and between groups. Separate models will be specified for child developmental outcomes (eg, motor, cognitive, and social-emotional), movement behaviors (eg, physical activity, sedentary time, and sleep), caregiver attitude and support measures, and educator-reported measures (eg, job satisfaction, health and well-being, and attitudes toward outdoor play). Models will include fixed effects for time (eg, T0 and T1), group (experimental vs usual care), and relevant covariates (eg, child age, sex, disability status, race and ethnicity, parent income, parent education, and newcomer status). For covariates with small subgroup sizes, distributions will be examined prior to modeling; where sparse categories are identified, categories will be collapsed as appropriate to ensure stable estimation. A random effect for participant (study ID) will be included to account for within-subject correlations across time points. The primary analyses will treat the 3 usual care sites as a single group. Sensitivity analyses will additionally adjust for the ELCC site (included as a fixed effect) to examine potential differences between individual usual care centers and to evaluate the extent to which such differences may influence the results.

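### Children are eligible from 10 months in both groups, but infants have only a thin, single-center usual-care comparator, and neither matching on total number nor an age covariate repairs this

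*Protocol article*

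**What the plan says.** Protocol article, Participants and Settings: dyads are eligible if "children are between the ages of 10‐59 months at baseline", with the same range for both groups. The experimental center has a separate infant class: "The infant group (<18 months) outdoor space is located closer to the building".

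The three usual-care centers are described by licence, in the same section. The apartment-building center "is licensed for 49 children (10 infants, 15 toddlers, and 24 preschoolers"; the church-basement center "is licensed for 39 children (15 toddlers and 24 preschoolers"; the suburban center "is licensed for 31 children (15 toddlers and 16 preschoolers". Only the first lists infants.

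The sample-size paragraph sets the recruitment aims: "we aim to enroll 100% of children attending the outdoor-focused ELCC center" and "seek to match this number across the usual care sites". It gives no age-specific target.

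The data analysis plan uses mixed models with fixed effects for time, group and "relevant covariates (eg, child age, sex, disability status, race and ethnicity, parent income, parent education, and newcomer status". The effect of interest is group by time. The plan says that having baseline among the repeated outcomes inherently adjusts for baseline differences. Strengths and Limitations similarly says that analyzing change inherently accounts for individual differences.

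**The concern.** The age range in the objective is wider than the range the usual-care centers can supply in any number. Recruiting more toddlers and preschoolers would meet the aim of equal totals and leave the infant gap as it is.

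This matters if six-month change on a measure depends on age. The experimental group would then contain more children in the youngest part of the growth curve, and the difference in growth would appear in group by time as if the program had caused it. Age adjustment by a main effect shifts levels; it does not let the rate of change differ by age. Where few usual-care children were observed, a richer age model extrapolates. At stake are the group-by-time estimates for the measures given to infants, and the claim that the comparison covers 10 to 59 months.

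**Working it through.** **Inputs.** Licensed places: 49 (10 infant), 39 (0 infant), 31 (0 infant). Infant means under 18 months at the experimental site; I assume the same cutoff for the usual-care licences, since all centers share the same provincial regulations. Table 2 ages: experimental 28.4 (SD 12.0), N = 54; usual care 32.4 (SD 6.9), N = 32.

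**1. Infant places in usual care (exact).** 49 + 39 + 31 = 119, and 10/119 = 8.4%, all at one center. Enrollment in proportion to licence would give 43 × 10/119 = 3.6 infants among the 43 usual-care children now enrolled, or 67 × 10/119 = 5.6 if the experimental total of 67 were matched.

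**2. Expected children under 18 months in Wave 1 (estimated).**

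| Assumed age distribution | Experimental, of 54 | Usual care, of 32 |
|---|---|---|
| Normal: Φ((18 − mean)/SD) | Φ(−0.87) = 0.193, so 10.4 | Φ(−2.09) = 0.018, so 0.6 |
| Normal cut at 10 and 59 months, Table 2 values used as its parameters | 0.140, so 7.6 | 0.018, so 0.6 |
| Truncated normal refitted so that its mean and SD equal Table 2 | 0.235, so 12.7 | 0.018, so 0.6 |

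The second row is a low figure only: once cut, that distribution has mean 29.8 and SD 10.3 in the experimental group, which does not agree with Table 2. For usual care the one-sided Chebyshev bound is 6.9²/(6.9² + 14.4²) = 0.187, or 5.98 of 32, so at most 5 children whatever the distribution. No such bound gives a minimum for the experimental group, so 8 to 13 rests on the assumed shape.

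**3. What an age main effect leaves behind.** Suppose change over six months is larger by d in children under 18 months than in older children, equally in both groups and with no program effect. The between-group difference in mean change is then (experimental share − usual-care share) × d:
- Normal: (0.193 − 0.018)d = 0.175d.
- Lowest and highest rows: (0.140 − 0.018)d = 0.12d and (0.235 − 0.018)d = 0.22d.

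The article does not give d. For an assumed d of 0.5 to 1 SD, the normal case gives about 0.09 to 0.17 SD, and the whole range is 0.06 to 0.22 SD. The study is planned around a small effect (f = 0.20). If d is zero, for example because an age-normed score removes the age trend, the term vanishes.

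**4. How long the gap lasts.** A child entering at 10 to 17 months is 16 to 23 months at T1 and 22 to 29 months at T2. By T2 every such child is in the toddler age range.

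**5. Which measures are affected.** The Nine-Hole Peg Test, S-TUG, grip strength and executive-function tasks start at 36 months, and the ECDI at 24 months. The gap falls on the PDMS-3, ASQ-3, accelerometry and anthropometry.

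**6. Children aged 18 months or older at first assessment.** Normal: 86 − 10.4 − 0.6 = 75. Refitted: 86 − 12.7 − 0.6 = 72.7. These are the two distributions consistent with Table 2, so about 73 to 75 of 86. The low row would give 86 − 7.6 − 0.6 = 77.8.

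**The case against.** A reader might infer that experimental infants have no counterpart at all. The documents do not support that. One usual-care center has 10 infant places, the cohort is open, and those places can refill over three years. The gap is also short: by T2 these children are at ages every center serves, and many of the direct tests are not given to infants. All of this stands and limits the point to baseline and early change on four measures.

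It also stands that the infant counts are modeled, and that Table 2 needs care: the usual-care sex counts sum to 22 of 32. With 22 children the normal estimate would be 22 × 0.018 = 0.4, which does not alter the contrast. The older end is uneven too, as usual-care ages have an SD of only 6.9, and an 18-month limit does not address that.

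It can be said that equal totals are an enrollment aspiration rather than a balancing method, that age adjustment is planned, and that overlap checks belong in a fuller plan. A fuller plan may hold such checks. But the published model and the two statements that analyzing change inherently handles baseline and individual differences are given as sufficient, and they are not when expected change depends on age. The site sensitivity analysis does not help either, since all usual-care infant places are in one center.

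Removing everyone who entered under 18 months from the primary comparison would go too far, because it discards their later, overlapping observations.

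**Conclusion.** The concern holds in a limited form. The licence counts are exact: 10 of 119 usual-care places are for infants, in one center, and no age-specific recruitment is stated. The Wave 1 imbalance, about 8 to 13 of 54 against about 1 of 32, is an estimate from the Table 2 means and SDs. The group-by-time estimate for the PDMS-3, ASQ-3, accelerometry and anthropometry can be biased by roughly 0.12 to 0.22 times any excess early growth under 18 months; the size of that excess, and which score is modeled, are not given. The between-group conclusion below 18 months is weakly supported rather than unsupported. The sample-size figure of 42 is not affected.

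**What to change.** One of three waves is complete, so recruitment and wording can still change:

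1. For the remaining waves, seek usual-care enrollment by licensed age room (infant, toddler, preschool), not by total only, within the 10 infant places.
2. For the four affected measures, add an age-at-entry by time term to the model.
3. Prespecify a between-group analysis restricted to observations made at 18 months or older, the range that all the usual-care centers license. Keep the later observations of children who entered as infants.
4. Report results under 18 months descriptively, and state that the between-group conclusion at that age rests on one usual-care center.
5. Qualify the two statements that modeling change inherently accounts for baseline and individual differences: this does not hold where expected change depends on age.

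The cost is protocol wording, some recruitment effort, slightly less precision in the restricted analysis (by estimate about 73 to 75 of 86 Wave 1 children were already 18 months or older at first assessment, and the others join it later) and a narrower age claim. No child leaves the study. Item 1 can improve the infant comparison only up to the licence limit.
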